### Trial design {8}

This study is a multi-center, randomized, placebo controlled, superiority trial. Stratified randomization allocates participants to four parallel intervention groups with a ratio of 1:1:1:1.

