#### Intervention description {11a}

All participants will be randomly allocated to one of four interventions for a total of 24 weeks; see Table 1.

**Table 1 Tab1:** Allocation groups

	***Allocation group***	***Active daily dose***	***Intake***
A	Magnesium citrate	350 mg^a^	3 dd 117mg
B	Placebo	x	3 dd 117mg
C	Magnesium citrate + SFOH	350 mg^a^, 1000 mg	3 dd 117mg + 2 dd 500mg^b^
D	Placebo + SFOH	x, 1000 mg	3 dd 117mg + 2 dd 500mg^b^

*SFOH* sucroferric oxyhydroxide, *dd* de die (per day)

^a^350 mg elemental magnesium, ^b^the SFOH intervention starts with one week of 1 dd 500 mg

Each allocation group receives one double blind intervention: magnesium citrate or matching placebo. Two allocation groups additionally receive the open label SFOH intervention.

The magnesium citrate and matching placebo capsules are prescribed thrice daily. Each magnesium citrate capsule contains 117 mg of elemental magnesium (magnesium citrate complex of 17.8%), resulting in a daily dose of 350 mg (14 mmol) magnesium. Magnesium citrate has a good bioavailability compared to other formulations and the laxative effect of magnesium citrate is limited [46]. To optimize absorption, the daily dose of 350 mg magnesium is distributed over the day, and this dosage is based on an intervention study that demonstrated a clinically relevant improvement of arterial stiffness after 24 weeks of supplementing 350mg magnesium citrate in slightly obese but healthy participants [17]. The magnesium citrate supplements and placebo are produced as one batch by Laboratory Medisan (Heerenveen, the Netherlands). Each package of magnesium citrate or placebo is labeled with a unique code that was randomly assigned by Laboratory Medisan accompanied with an identification list that was provided to the research pharmacies.

Participants that are randomized to arm C or D are requested to take the SFOH chewing tablet of 500 mg at the beginning of their two largest meals of the day. In order to limit potential gastro-intestinal side effects, participants start the first week of the intervention with SFOH 500 mg once a day whereafter they continue with twice daily 500mg for the remaining 23 weeks. A dose of 1000 mg/day is adequate in lowering phosphate levels in case of hyperphosphatemia [47] and could prevent phosphate from increasing over time without considerable risk of hypophosphatemia.

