#### Implementation {16c}

After initial approach by their treating physician, participants will be enrolled by one of the researchers. After informed consent and screening, participants are allocated by the research pharmacies through ALEA software. A subsample of the first 40 participants who met additional inclusion criteria and gave their consent for nuclear imaging will be randomized to undergo either explorative ^18^F-FDG or ^18^F-NaF PET-scan imaging at the VUmc. To ensure five participants of each nuclear tracer in all four intervention groups, this randomization is performed manually (i.e. an envelope for each allocation arm, including 5 PET-scan tickets for each tracer) by an independent research nurse with access to the ALEA randomization results.

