### Statistical methods

#### Statistical methods for primary and secondary outcomes {20a}

Patient characteristics will be presented by treatment arm as mean ± standard deviation (SD) or median with an interquartile range (IQR) for normally and non-normally distributed continuous data, respectively. Categorical variables will be presented as number and percentage. Differences between treatment arms will be visually inspected for clinically relevant differences.

The primary and secondary endpoints will be analyzed with linear mixed models, with repeated measurements (at baseline, 12 weeks, and 24 weeks) and random intercepts at patient level. In case of non-normally distributed residuals of the outcome variables, suitable transformation (e.g., logarithmic) will be performed. Based on the −2 log likelihood evaluation, additional center level and random slopes will be added to the analysis when needed. The main analysis will focus on the three active intervention groups separately, in comparison to the placebo. Also, the additional value of the combined intervention of magnesium citrate and SFOH will be analyzed compared to solely magnesium citrate and SFOH supplementation by coding the magnesium citrate and SFOH as reference category, respectively. Due to stratified randomization, these important confounders are expected to be evenly distributed between the intervention groups. However, confounding by baseline differences of age, sex, eGFR, Kauppila index, baseline plasma magnesium, and phosphate concentrations will be considered in case of clinically relevant or ≥ 10% difference between groups. To evaluate when the effect of the intervention occurs at its maximum, an interaction term for both categorical time variables (12 and 24 weeks versus baseline) will be evaluated in the analysis for primary and secondary outcomes.

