#### Methods for additional analyses (e.g., subgroup analyses) {20b}

The intervention effect on plasma magnesium and phosphate and their urinary excretion will be analyzed with linear mixed models with repeated measurements and linear regression analysis, respectively. Subgroup sensitivity analyses will be reported for the stratified eGFR, Kauppila index, sex, median age, blood pressure, presence of diabetes, median baseline magnesium, and phosphate levels and proton pump inhibitor or diuretic use to test the robustness of the analysis. In addition, for the primary endpoint of PWV, the mediating effect by plasma magnesium and phosphate levels, blood pressure, T_50-_test, CPPs, α-klotho, and cFGF-23 will be explored using causal mediation analysis.

The analysis of the explorative ^18^F-NaF and ^18^F-FDG PET-scans will be based on the axial regions of interest (ROI). Differences between the intervention groups in standardized uptake value (SUV), target to background ratio (TBR), and most diseased segment (MDS) will be analyzed with linear regression analysis, with adjustment for baseline value.

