## Discussion

This study is the first multi-center, randomized controlled trial assessing the combined effect of magnesium citrate and the phosphate binder SFOH on arterial stiffness, calcification, and inflammation parameters in people with stage 3 and 4 CKD, based on the understanding that increasing magnesium and improving phosphate homeostasis could synergistically retard the progression of established vascular calcification [19], and people with moderate CKD could benefit most. To our knowledge, only two oral magnesium intervention studies in patients with moderate CKD have been performed so far [53, 54]. A 2-year open-label randomized trial in stage 3–4 CKD patients demonstrated a statistically significant smaller median increase in coronary artery calcification (11.3% versus 39.5%) for participants treated with magnesium oxide as compared to the control group [53]. Another RCT in a comparable population with moderate CKD resulted in a significant increase (improvement) of T_50_ of 40 min (95% confidence interval 11–70 min, *P* <0.05) compared to placebo, after 8 weeks of oral magnesium hydroxide supplementation [54]. Different form the established effects of phosphate binders on correcting hyperphosphatemia, these effects of phosphate-lowering therapy in moderate CKD in the absence of hyperphosphatemia are not yet well established [43–45, 55, 56]. In this study, the non-calcium based phosphate binder SFOH is prescribed because of its relatively low pill burden compared to other phosphate binders [47] and to avert the potential confounding effect on vascular calcification due to calcium content. The explorative ^18^F-FDG and ^18^F-NaF PET-scans will also contribute to the understanding of important pathophysiological mechanisms of arterial wall inflammation and calcification, respectively. A recent study in CKD patients without overt atherosclerotic disease observed increased arterial wall inflammation through ^18^F-FDG PET imaging, compared to healthy controls. ^18^F-NaF PET-scans conceivably enable microcalcification formation detection, even before macroscopic calcification is revealed through regular CT techniques. Moreover, the lack of ^18^F-NaF uptake in macroscopic calcified vessel walls supports the theory that ^18^F-NaF only binds to active calcification deposition and therefore studies an early or active phase of arterial calcification. It is in this early phase, that modulating magnesium and phosphate might prove most beneficial.

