Several clinical and preclinical studies support the potential of combined magnesium and phosphate interventions. In vitro, the presence of high magnesium levels can prevent the phosphate-induced phenotypic switch of vascular smooth muscle cells of the intima media into bone forming cells and additionally is an inhibitor of the formation of precipitating calcium-phosphate products (hydroxyapatite nanocrystals) [21, 57, 58]. In clinical setting, high magnesium concentrations are associated with lower calcification propensity (i.e., higher T_50_ values), inhibition of the phosphate containing CPP formation rate, and with lower FGF23 levels [54, 59].

Strengths of this study include the possibility to investigate magnesium citrate and sucroferric oxyhydroxide as modulators of vascular calcification synergically and separately on various parameters of interest. By additionally measuring the T_50_, we will be able to investigate if the presumed effect on arterial stiffness is mediated by calcification propensity. The study design with repeated measurements of primary and secondary outcomes allows for thorough statistical analyses and a reduced number of participants. This design also allows for studying the intervention effects over time, i.e., at 12 weeks, 24 weeks, and after a wash-out period. The main limitation of this study is the fact that arterial stiffness is only a intermediate marker of CVD and has some degree of operator dependency. However, the association of PWV and cardiovascular disease and mortality is well established in the CKD population [11–14], and intervention effects can be detected already after 6 months [17, 18]. The PWV measurements will be performed by a limited number of well-trained study personnel, aiming at measurements performed on an individual participant by the same operator, thereby limiting the effect of inter-operator variability.

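### The protocol presents its four arms as able to study synergy, but plans only pairwise contrasts and no magnesium-by-SFOH interaction estimate

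*Protocol article*

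**What the plan says.** Under Trial design {8}, "Stratified randomization allocates participants to four parallel intervention groups with a ratio of 1:1:1:1". Intervention description {11a} explains how the groups are built: "Each allocation group receives one double blind intervention: magnesium citrate or matching placebo. Two allocation groups additionally receive the open label SFOH intervention". Table 1 therefore holds all four combinations of magnesium (yes or no) and SFOH (yes or no), although the article never calls the design factorial.

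The Discussion gives as rationale that "increasing magnesium and improving phosphate homeostasis could synergistically retard the progression of established vascular calcification", and lists as a strength "the possibility to investigate magnesium citrate and sucroferric oxyhydroxide as modulators of vascular calcification synergically and separately".

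Statistical methods for primary and secondary outcomes {20a} sets out the comparisons. The main analysis takes A, C and D separately against B. In addition, "the additional value of the combined intervention of magnesium citrate and SFOH will be analyzed compared to solely magnesium citrate and SFOH supplementation", with A and D coded in turn as the reference category. The only interaction term named there is with time (12 and 24 weeks against baseline). Neither that section nor those on additional analyses {20b} and on non-adherence and missing data {20c} names a magnesium-by-SFOH term or contrast.

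**The concern.** Synergy means that the joint effect exceeds the sum of the separate effects. On the scale of the PWV change this is (C−D)−(A−B): the magnesium effect with SFOH minus the magnesium effect without it. C versus A is the SFOH effect in the presence of magnesium, and C versus D is the magnesium effect in the presence of SFOH. If the agents act independently and simply add, both contrasts differ from zero while the interaction is exactly zero.

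The article thus offers the design as a way to study synergy, but none of its five planned contrasts, with its confidence interval, addresses that question. Nor does it tell the reader how imprecise the answer would be, because the sample size is set for a two-arm comparison only.

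**Working it through.** **Inputs.** From Sample size {14}: difference 1.0 m/s, SD 2.0 m/s, correlation between baseline and follow-up 0.7, two-sided 5% level, 80% power, 38 per group, 15% drop-out, 45 per group and 180 in total. The interaction sizes of 1.0 and 0.5 m/s below are assumptions; the article gives none. Normal approximations are used throughout.

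**Step 1: reproduce the plan's figure.**
- Variance of the change score: 2 × 2.0² × (1 − 0.7) = 2.4, so SD 1.549 m/s.
- n per group = 2 × 2.4 × (1.960 + 0.842)² / 1.0² = 37.7, rounded up to 38. This matches.
- 38 / 0.85 = 44.7, rounded up to 45; 4 × 45 = 180. This matches.
- A baseline-adjusted variance, 2.0² × (1 − 0.7²) = 2.04, would give 33 per group, so the stated 38 rests on the change score.

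**Step 2: what C versus A and C versus D show under pure additivity.**
- SE of one pairwise contrast: √(2 × 2.4 / 38) = 0.355 m/s.
- Let each agent lower PWV by 1.0 m/s with no interaction, so the mean changes relative to B are A −1, D −1 and C −2. Each of the two contrasts then has about 80% power. In a simulation of 400,000 trials both were significant in 69%, while a test of the interaction rejected in 5%, its nominal level.
- Let each agent lower PWV by only 0.5 m/s, again with no interaction. Each contrast is significant with probability Φ(0.5/0.355 − 1.96) = 29%. The two estimates share arm C and so have correlation 0.5, which makes both significant in about 15% of trials.

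In either case two significant results are no evidence of synergy.

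**Step 3: precision of the interaction.**
- SE = √(4 × 2.4 / 38) = 0.503 m/s, which is √2 times that of a pairwise contrast.
- Half-width of the 95% CI: 1.96 × 0.503 = 0.99 m/s.
- Power for 1.0 m/s: Φ(1.0/0.503 − 1.96) = 51%. Power for 0.5 m/s: 17%.
- Interaction detectable with 80% power: 2.80 × 0.503 = 1.41 m/s.
- With baseline adjustment (variance 2.04): SE = √(4 × 2.04 / 38) = 0.463 m/s; power 58% for 1.0 m/s and 19% for 0.5 m/s; detectable interaction 1.30 m/s.
- For 80% power at 1.0 m/s: 4 × 2.4 × (2.802)² = 75.3, so 76 evaluable per arm (65 with baseline adjustment), against 38 planned.

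**The case against.** The strongest reply is that synergy is neither an objective nor an endpoint here. Objectives {7} asks about the combined use of the agents, Outcomes {12} compares active groups with placebo, and the methods section asks for the additional value of the combination. C versus A and C versus D answer that last question correctly. This stands: the planned contrasts are valid for what they are said to do, and nothing in the article announces that their results will be reported as synergy. What remains is that the Discussion claims the capability as a strength and no planned estimate supports it.

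A second reply is that the interaction equals (C−B)−(D−B)−(A−B), so the three main contrasts already fix its point estimate. That is true, but its standard error and confidence interval cannot be read from three separate intervals that share arm B, and they are not a planned output.

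A third is that an article may leave secondary contrasts to a fuller document. That would settle the matter if the article were silent. Instead it lists its contrasts down to the reference coding and makes a claim that they do not meet.

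Two stronger readings are tempting and are not supported.
- **That the plan wrongly omits pooled effects (A+C versus B+D, and C+D versus A+B).** These have a smaller SE, √(2.4/38) = 0.251 m/s, but they average one agent's effect over use of the other. They can be read as single-agent effects only if there is no material interaction, and the rationale expects one. Separate comparisons with placebo are a defensible choice.
- **That the PET analysis is confined to comparing five with five.** Implementation {16c} does say "To ensure five participants of each nuclear tracer in all four intervention groups", but section {20b} only outlines a baseline-adjusted regression of differences between the intervention groups. It does not exclude a two-factor model, and the scans are exploratory.

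**Conclusion.** The concern holds in a limited form. The five planned pairwise contrasts are sound for their own questions. The mismatch is between the claim that the agents can be studied for synergy and a plan with no magnesium-by-SFOH interaction estimate and interval. The main comparisons and the sample size are unaffected.

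Were the interaction estimated, it would be imprecise: a 95% CI of roughly ±1.0 m/s, and about even odds of detecting an interaction as large as the whole effect for which the trial was sized. These figures assume SD 2.0 m/s, correlation 0.7 and 38 evaluable per arm. The article plans to recalculate the sample size halfway through recruitment from the observed SD, correlation and drop-out, so they may change.

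**What to change.** Add to section {20a}, as a secondary or exploratory estimate from the same mixed model, the week-24 interaction (C−D)−(A−B) in the change of PWV with its 95% CI. State that any remark about synergy will rest on this estimate alone and not on C versus A or C versus D. State its expected precision under the design assumptions (SE about 0.50 m/s; power about 51% for 1.0 m/s, or 58% if baseline-adjusted, and 17% for 0.5 m/s), and update it if the sample size is revised. If the investigators do not want this estimate, the alternative is to reword the Discussion so that it claims only the added value of the combination over each single agent.

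The cost is one contrast from a model that will be fitted anyway, with no new participants or data. The drawback is one more low-powered estimate to report, whose wide interval must not be read as evidence that synergy is absent. Pooled effects for PWV or PET may be added as supporting summaries, with the no-interaction assumption stated, but they are not required.

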### Assignment of interventions: allocation

#### Sequence generation {16a}

The randomization procedure is performed by the research pharmacy with ALEA software (version 16) with stratification for the eGFR at screening of < or ≥ 30ml/min/1.73m2 and a Kauppila index of < or ≥5. The Kauppila index is determined at the run-in visit by a lateral lumbar radiography depicting presence of calcification in the abdominal aorta [51].

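### The two stratification factors are not fixed in the primary model; adjustment depends on observed baseline imbalance, a trigger driven by scale and chance that stratification makes unlikely to fire for the strata themselves

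*Protocol article*

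**What the plan says.** Under Sequence generation {16a}, the protocol article specifies "stratification for the eGFR at screening of < or ≥ 30ml/min/1.73m2 and a Kauppila index of < or ≥5".

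Under Statistical methods {20a}, primary and secondary endpoints are analysed by linear mixed models "with repeated measurements (at baseline, 12 weeks, and 24 weeks) and random intercepts at patient level". No fixed covariate is named. The section continues: "Due to stratified randomization, these important confounders are expected to be evenly distributed between the intervention groups". It then lists six candidate covariates (eGFR, Kauppila index, age, sex, magnesium and phosphate) and says of possible confounding by them that it "will be considered in case of clinically relevant or ≥ 10% difference between groups". Baseline imbalance is judged by eye: "Differences between treatment arms will be visually inspected for clinically relevant differences". Part of the remaining structure is also left to the data, by a likelihood comparison: "additional center level and random slopes will be added to the analysis when needed".

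The only other use of the strata in the analysis is as subgroup factors, under Methods for additional analyses {20b}.

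**The concern.** The reasoning runs the wrong way. Stratified allocation removes between-arm variation due to the strata. If the strata predict the analysed outcome and the model omits them, that variance stays in the error term and the standard error is too large. Expected balance is therefore a reason to include the strata, not to leave them out. Because stratification keeps them balanced, an imbalance trigger is least likely to fire for the very factors the design calls for.

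The trigger is also not reproducible. The article does not say whether 10% is absolute or relative, which pairs of the four arms count, or how it applies to a skewed score. The alternative route, clinical relevance, is a judgement made after seeing the baseline table, and to consider adjustment is not to commit to it. The primary model could thus differ with the draw of the baseline data. At stake are some power and a primary model that is not fixed in advance.

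**Working it through.** **1. The plan's own figure.** Inputs from Sample size {14}: difference 1.0 m/s, SD 2.0 m/s, rho 0.7, two-sided 0.05, power 80%, drop-out 15%.
- SD of change = 2.0 × √(2 × (1 − 0.7)) = 1.549.
- n per arm = 2 × (1.960 + 0.842)² × 1.549² / 1.0² = 37.7, so 38.
- 38 / 0.85 = 44.7, so 45; 4 × 45 = 180.

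The stated 38, 45 and 180 are reproduced as a comparison of change scores. The point concerns the model, not the sample size.

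**2. How often chance alone meets a 10% trigger.** Simulation with four arms of 45, counting trials in which at least one of the three active arms differs from placebo by 10% or more. The documents give no baseline distributions, so all of these are assumptions.

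| Covariate (assumed) | Reading of 10% | Trials triggered |
|---|---|---|
| Sex, 60% male | percentage points | about 64% |
| Sex, 60% male | relative | about 90% |
| Age, mean 63, SD 12 | relative, means | 3% to 4% |
| Magnesium, mean 0.85, SD 0.10 | relative, means | about 0% |
| eGFR, mean 32, SD 9, allocation not stratified | relative, means | 22% |
| eGFR, same, permuted blocks stratified at 30 and by Kauppila | relative, means | about 2% |
| eGFR, same, stratified and limited to the eligible 15 to 50 | relative, means | about 0.4% |

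The stratified rows assume blocks of 4 or 8 and an even Kauppila split. For continuous covariates without stratification, the rate follows the coefficient of variation: about 0% to 1% at 0.10 to 0.15, about 26% at 0.30 and about 66% at 0.50. None of these rates reflects how well a covariate predicts PWV.

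**3. Cost if the strata predict the analysed outcome.** Let R² be the share of variance in PWV change explained by the strata (assumed).
- SE overstatement = 1/√(1 − R²) − 1: 5.4% at R² = 0.10, 20% at R² = 0.30.
- Type I error = 2 × (1 − Φ(1.96/√(1 − R²))): 3.9% at 0.10, 1.9% at 0.30.

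Simulation of linear models, two arms of 38, stratified permuted blocks, standardised effect 1.0/1.549, R² from 0.10 to 0.30:

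| Model | Type I error | Power |
|---|---|---|
| Unadjusted | 0.040 to 0.020 | 0.80 to 0.83 |
| Adjusted only if arms differ by 10 points | 0.041 to 0.020 | 0.79 to 0.82 |
| Strata always included | 0.047 to 0.051 | 0.83 to 0.91 |

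**4. Cost if the strata predict only PWV level.** With the stratum explaining 30% of level variance but none of the change, the unadjusted change test had a type I error of 5.0%. In one fitted random-intercept model with complete data, adding a time-constant covariate as a main effect left the arm-by-time estimate at the last visit unchanged (−0.829, SE 0.339 both ways). In a model without the interaction, the arm effect moved from −0.293 to −0.424. So a main effect does not act on the change contrast; a covariate-by-visit term is needed.

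**The case against.** The strongest reply is that the primary endpoint, under Outcomes {12}, is a difference in change. Strata that predict only level are absorbed by the within-patient comparison, so leaving them out costs nothing there, and data-driven main-effect adjustment barely moves the 24-week contrast. This stands, and it limits the loss to the case in which the strata predict change. The documents give no figure for that. The protection also depends on the arm-by-visit term being the primary effect; the article introduces that interaction to find when the effect is largest and does not say clearly whether it or an overall arm effect is primary.

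Three stronger readings that a reader might infer are not supported:
- *The rule inflates false positives.* The calculations show a conservative test where the strata matter and no inflation under conditional adjustment.
- *The plan ignores its design, or adjusts only at 10%.* Both strata are named candidate covariates and subgroup factors, and clinical relevance is a second route that could catch a small relative difference, in magnesium for instance.
- *Mean eGFR would often trip the rule.* The 22% rate needs unstratified allocation, which is not this design.

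Blinding also counts for the plan. The sections on concealment {16b}, blinding {17a} and statistical methods have the analysis done on coded groups before the code is revealed, and the six candidates are listed in advance. That limits steering towards a preferred result. It does not fix the model, and SFOH is open-label.

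**Conclusion.** The point holds as a moderate one that should be changed. The text leaves the strata out of the primary model by default, for a reason that argues for including them, and lets observed imbalance decide the covariates. The trigger rates rest on assumed baseline distributions, and the precision loss on an assumed 10% to 30% of the variance in PWV change explained by the strata. In that range, type I error falls to about 4% to 2%, and power is about 0.79 to 0.82 under conditional adjustment against 0.83 to 0.91 with the strata always included. If the strata predict level only, the effect on the 24-week change contrast is essentially nil. The size of the loss is therefore uncertain; the dependence of the model on the data is not.

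**What to change.** Delete the imbalance trigger from the primary analysis. In the primary and all secondary mixed models, always include the two stratification factors as randomised (eGFR below 30 or from 30; Kauppila index below 5 or from 5), each with its interaction with visit so that the adjustment acts on the change contrast. Confine adjustment for any other covariates to a sensitivity analysis, with the covariates named in advance. Requiring age and sex in the primary model would be a preference; nothing in the article shows that they predict change in PWV.

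The cost is a wording change, to be settled before the code is revealed, and a few degrees of freedom out of 180 participants. Both factors are already collected for randomisation, and the sample size is unchanged.

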#### Outcomes {12}

The primary endpoint of the study is difference in change of PWV over 24 weeks between the active intervention groups compared to the placebo group. PWV is measured at baseline and 12 and 24 weeks, with the SphygmoCor v9 (AtCor Medical, Sydney Australia). Before measurement of the PWV, blood pressure measurements in supine position are repeatedly performed until the blood pressure stabilizes with a maximum systolic difference of ≤ 3mmHg. The carotid-femoral PWV is measured at least twice during these corresponding visits, with a tonometer and simultaneous ECG recording. The carotid-femoral transit time is automatically calculated based on the delay of the pulse wave arrival at carotid and femoral measurement sites in relation to the ECG R-wave. Subsequently, the PWV is calculated using this carotid-femoral transit time and the travel distance between the carotid artery and femoral artery measurement sites. The travel distance is assessed as the direct carotid-femoral distance (in mm) * 0.8, as is recommended in a PWV expert consensus document [49]. Each measurement is evaluated based on strict quality criteria and the average of two good quality measurements is taken (see Additional file 1).

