#### Sample size {14}

The sample size of this study is based on the primary endpoint. A 1.0 m/s difference in PWV is clinically relevant and can be expected with a magnesium intervention of 24 weeks in healthy subjects and a CKD population with accelerated CVD risk [11, 17]. Based on prior studies on arterial stiffness in populations with CKD stages 1–5, with mean PWV values between 10.5 and 12.0 m/s and a standard deviation (SD) of 1.4-3.5 m/s [10, 12, 13], we assume for our study population with an eGFR 15–50 ml/min/1.73m^2^ a SD of 2.0 m/s. With a statistical power of 80%, a two-sided significance of 0.05 and a rho of 0.7 to account for the correlation between baseline and follow-up measurements, 38 participants are required per group. To account for an anticipated drop-out rate of 15% during the 24 weeks, a total of 180 CKD patients will be included and randomized in a ratio of 1:1:1:1, with 45 participants in each intervention group. In case of an unexpected high drop-out rate (> 15%) for reasons not related to study participation (for example starting dialysis, transplantation, referral to a non-participating center), then additional participants can be recruited.

The sample size calculation was performed with the PASS 15.0.5 software and a statistical consultant.

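### The terms named for finding the time of maximum effect each compare one visit with baseline, so neither compares the effect at 12 weeks with the effect at 24 weeks

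*Protocol article*

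**What the plan says.** All of the following is in the Protocol article.

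- **Model** (Statistical methods {20a}): "linear mixed models, with repeated measurements (at baseline, 12 weeks, and 24 weeks) and random intercepts at patient level".
- **Comparisons** (same section): "The main analysis will focus on the three active intervention groups separately, in comparison to the placebo".
- **Timing** (same section): the aim and the tool stand in one sentence, "when the effect of the intervention occurs at its maximum, an interaction term for both categorical time variables (12 and 24 weeks versus baseline"). This applies to the primary and the secondary outcomes. The sentence says the term will be evaluated, but not whether by P value, by size of estimate or otherwise. No contrast of week 24 with week 12 is named there or elsewhere.
- **Primary endpoint** (Outcomes {12}): "difference in change of PWV over 24 weeks between the active intervention groups compared to the placebo group".
- **Reading of results** (Statistical methods {20a}): P<0.05, two-sided, applies to the primary endpoint. Secondary endpoints are to be read mainly from estimates and confidence intervals.
- **Discussion**: timing is listed among the strengths, "This design also allows for studying the intervention effects over time, i.e., at 12 weeks, 24 weeks", and after wash-out.

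**The concern.** Asking when an effect is largest means asking whether it differs between visits, so the relevant null is equal effects at weeks 12 and 24. The named terms answer another question. With baseline as the reference, the week-12 term has the null of no effect at week 12, and the week-24 term has the null of no effect at week 24.

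One significant and one non-significant term does not show that the two effects differ, and neither does one estimate being larger than the other. A reader of the results could be told that the benefit wanes after week 12, or is still growing at week 24, on a comparison that does not address either statement. The same sentence covers PWV and the secondary outcomes, with three active arms each set against placebo.

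**Working it through.** **Inputs.** From Sample size {14}: "A 1.0 m/s difference in PWV is clinically relevant"; SD 2.0 m/s; "With a statistical power of 80%, a two-sided significance of 0.05 and a rho of 0.7"; "38 participants are required per group"; drop-out 15%. Not given: the correlation between weeks 12 and 24. I take 0.7, which is what a random-intercept model implies if rho is 0.7, and vary it. Effects are given as absolute sizes.

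**1. Reproduce the plan's figure.** SD of change = 2.0 × √(2 × (1 − 0.7)) = 1.549 m/s. n = 2 × (1.960 + 0.842)² × 1.549² / 1.0² = 37.7, so 38 per group, as stated. 38 / 0.85 = 44.7, so 45 per group and 4 × 45 = 180, as stated.

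**2. What each term tests.** Let b12 and b24 be the differences (active minus placebo) in change from baseline at weeks 12 and 24.
- Arm-by-week-12 term: null b12 = 0.
- Arm-by-week-24 term: null b24 = 0.
- Joint test of both: null b12 = b24 = 0.
- The timing question: null b24 − b12 = 0, which none of these tests.

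**3. Standard errors at 38 per arm.** SE(b12) = SE(b24) = √(2 × 1.549² / 38) = 0.355 m/s. Their correlation is (0.7 − 0.7 − 0.7 + 1) / (2 × (1 − 0.7)) = 0.3 / 0.6 = 0.5. At an effect of 1.0 m/s, each term has 80% power.

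**4. If timing were read from significance.** Two million bivariate-normal draws for one active arm versus placebo, with the same true effect at both visits:

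| Setting | Exactly one term significant |
|---|---|
| 1.0 m/s | 22% |
| 0 m/s | 8% |
| 0.5 m/s | 28% |
| 0.7 m/s | 33% |
| 1.3 m/s | 7% |
| 1.0 m/s, 12-to-24-week correlation 0.8 | 18% |
| 1.0 m/s, 12-to-24-week correlation 0.9 | 13% |
| 1.0 m/s, all correlations 0.5 | 33% |
| 1.0 m/s, all correlations 0.8 | 10% |
| 1.0 m/s, 45 per arm | 17% |

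The first row follows from 80.3% + 80.3% − 2 × 69.2% (both significant) = 22.2%. The splits fall equally on the two visits. In 400 simulated trials fitted with a random-intercept mixed model at 1.0 m/s, the rate was 22.5%. Over three active arms sharing one placebo, at least one split occurs in 47% of trials at 1.0 m/s.

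**5. If timing were read from the larger estimate.** One visit is always named. Under equal true effects, the mean absolute gap between the two estimates is 0.355 × √(2/π) = 0.28 m/s, from chance alone.

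**6. The direct contrast.** SE(b24 − b12) = √(2 × 2 × 4 × (1 − 0.7) / 38) = 0.355 m/s. Under equal effects it rejects in 5.0% of draws (4.5% in the fitted models). Its power is 29% for 0.5 versus 1.0 m/s and 80% for 0 versus 1.0 m/s.

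**The case against.** The strongest reply is that the plan states no decision rule. It says the terms will be evaluated. It does not say that a peak is declared when one is significant and the other is not, or that the larger one wins. The rates in step 4 belong to the first of these rules and the statement in step 5 to the second. This stands, and it limits what the figures show: they describe what can happen if the terms are read separately, not what the plan commits to.

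It is also true that the model is the right one. Categorical visits crossed with arm are what a timing question needs, and the missing contrast is the difference of two coefficients already in the model. The Discussion sentence speaks of effects at each visit, which the terms do estimate, and makes no claim about a maximum. For secondary endpoints, the emphasis on estimates and intervals makes a reading from P values less likely.

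One could add that a condensed article may leave such a contrast to an analysis plan. That carries less weight here, because the article is not silent. It pairs a specific aim with specific terms and a specific coding, and those terms taken separately do not meet the aim. Separate confidence intervals for b12 and b24 do not help either, since neither is an interval for their difference.

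**Conclusion.** The point holds in a limited form: the tool named for the timing question does not answer it, and reading the two terms separately can suggest a peak where there is none. At the design effect, a split in significance arises in about 22% of comparisons, and in roughly 7% to 33% over the cases tried. These figures rest on the plan's own SD, rho and sample size, on the assumed 12-to-24-week correlation, and on timing being read from significance.

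Three stronger readings are tempting, and the document supports none of them.
- That the analysis will produce a false peak: even under a significance rule most comparisons show no split, and only the larger-estimate rule always names a visit.
- That false peaks will be reported for every secondary outcome: no reporting rule of that kind is stated, and the simulation uses PWV inputs only.
- That the mixed model or the main result is compromised: the 24-week primary comparison is a separate matter, and the sample size reproduces exactly.

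**What to change.** In Statistical methods for primary and secondary outcomes {20a}, complete the timing sentence along these lines: *The timing of the effect will be judged from the difference in treatment effect between week 24 and week 12 for each active arm versus placebo, estimated from the same arm-by-visit model and reported with its 95% CI. No peak will be inferred from comparing the two baseline-referenced terms separately.*

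This costs one sentence and one linear contrast, with no new model, visits or participants. The downside is the contrast's low power (step 6), so the honest report will often be that the effects at 12 and 24 weeks cannot be told apart. Whether to go further and require the interval to exclude zero before any statement on timing is a matter of preference and is not needed for the correction.
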